## Abstract

**Simple Summary:**

Women with disease-causing gene changes (faults/mutations) in *BRCA1, BRCA2, PALB2*, *CHEK2* and *ATM* are at an increased risk of developing certain types of cancer—specifically breast (all genes) and epithelial ovarian cancer (only *BRCA1, BRCA2, PALB2*). At present, the risk estimates given to women by most healthcare professionals are broad (e.g., 35–85% lifetime risk of breast cancer for *BRCA1* and *BRCA2*) and are not personalised. This can make it difficult for women to make informed decisions regarding the risk-management options available to them. By combining information about genetic, lifestyle and hormonal risk factors, we can produce a narrower, more personalised risk estimate (e.g., 44% lifetime risk of breast cancer). In this study, we aim to test whether offering personalised risk estimates to women undergoing predictive testing in genetics centres in the UK and USA better supports women’s mental health and choices about their clinical care, relative to standard care. In addition, we will explore the experiences of both staff and women taking part in the study, to understand whether personalised risk estimates are acceptable, feasible and cost-effective for use in clinical care.

**Abstract:**

Women who test positive for an inherited pathogenic/likely pathogenic gene variant in *BRCA1, BRCA2, PALB2*, *CHEK2* and *ATM* are at an increased risk of developing certain types of cancer—specifically breast (all) and epithelial ovarian cancer (only *BRCA1, BRCA2, PALB2*). Women receive broad cancer risk figures that are not personalised (e.g., 44–63% lifetime risk of breast cancer for those with *PALB2*). Broad, non-personalised risk estimates may be problematic for women when they are considering how to manage their risk. Multifactorial-risk-prediction tools have the potential to deliver personalised risk estimates. These may be useful in the patient’s decision-making process and impact uptake of risk-management options. This randomised control trial (registration number to follow), based in genetic centres in the UK and US, will randomise participants on a 1:1 basis to either receive conventional cancer risk estimates, as per routine clinical practice, or to receive a personalised risk estimate. This personalised risk estimate will be calculated using the CanRisk risk prediction tool, which combines the patient’s genetic result, family history and polygenic risk score (PRS), along with hormonal and lifestyle factors. Women’s decision-making around risk management will be monitored using questionnaires, completed at baseline (pre-appointment) and follow-up (one, three and twelve months after receiving their risk assessment). The primary outcome for this study is the type and timing of risk management options (surveillance, chemoprevention, surgery) taken up over the course of the study (i.e., 12 months). The type of risk-management options planned to be taken up in the future (i.e., beyond the end of the study) and the potential impact of personalised risk estimates on women’s psychosocial health will be collected as secondary-outcome measures. This study will also assess the acceptability, feasibility and cost-effectiveness of using personalised risk estimates in clinical care.

## 1. Introduction

Women with pathogenic variants (PVs) in cancer-predisposing genes such as *BRCA1, BRCA2, PALB2*, *CHEK2* and *ATM*, have an increased risk of developing breast cancer (BC), and those with PVs in *BRCA1, BRCA2* and *PALB2* also have an increased risk of epithelial ovarian cancer (EOC), which is the representative histological type of hereditary ovarian cancer for these genes [1]. Current risk estimates given to women for the three breast/ovary genes range from 35–85% lifetime risk for BC and 5–60% lifetime risk for EOC [2]. Furthermore, the risk estimates given to women have a broad range (e.g., 65–79% lifetime risk for BC in *BRCA1*), and do not currently consider personal genetic/lifestyle/hormonal modifiers, even though they are known to influence risk [3,4,5,6,7].

The clinical management of women with high-risk PVs (i.e., *BRCA1/2* and *PALB2*) includes enhanced surveillance, chemoprevention and risk-reducing surgery [8]. For moderate-risk PVs (i.e., *CHEK2* and *ATM)*, the emphasis is more on surveillance and chemoprevention than surgical-risk reduction. Whilst interventions such as chemoprevention, bilateral risk-reducing mastectomy (BRRM) and risk-reducing bilateral salpingo-oophorectomy (RRBSO) can significantly reduce the risks of breast and/or EOC, they require careful consideration, including balancing the risks of developing a potentially life-threatening cancer as well as the potential physical and psychological side effects [9,10,11,12,13,14,15].

Multifactorial-risk-prediction models (e.g., BOADICEA [16,17]) give personalised risk estimates in the general population, in women with cancer family history and those with moderate- and high-risk PVs [18]. These comprehensive risk models combine information about the PV and other genetic and non-genetic modifying factors, such as polygenic risk score (PRS), family history, lifestyle (age at first pregnancy, oral contraceptive pill use, BMI, alcohol consumption) and mammographic density (where available). Clinical tools, such as CanRisk (www.canrisk.org 30 May 2022 [19]), have been designed and tested to support the use of BOADICEA [16] and the associated ovarian-cancer model [17] in clinical practice [20].

Personalised risk estimates may have an important role in supporting women to make informed decisions about their clinical care, as the level of risk (clinical or perceived) has been shown to affect the uptake of risk-management options [21,22,23,24]. In some cases, personalised risk estimates will identify those who might benefit from more intensive early-detection strategies (i.e., those at particularly high lifetime risk, or those with a high cancer risk at an early age). For instance, a *CHEK2* or *ATM* carrier is generally quoted a lifetime risk of 20–30% and not offered BRRM. However, for those carriers with a strong family history of breast cancer and additional risk factors, CanRisk will generally give a lifetime risk of >35%, which would mean discussing BRRM, in accordance with the UK NICE guidelines [25]. Conversely, personalised risk estimates will also identify women with PVs at much lower risk who could then opt to delay or not undergo risk-reducing surgery or chemoprevention. Either way, personalised risk estimates will likely provide healthcare professionals with more nuanced information about their patient’s cancer risk, which may be helpful in the counseling process [14,16].

Whilst multifactorial-risk-prediction tools are now available and recommended for use in clinical practice [25], the availability and impact of personalised risk estimates on women with PVs in moderate/high-risk genes is currently unknown. We anticipate personalised risk estimates may support women to make informed decisions about the uptake of appropriate risk management options, and exploring the potential impact of personalised risk estimates on women’s psychosocial health (i.e., cancer worry, anxiety, quality of life) is also essential. Similarly, evidence on the acceptability, feasibility and economic impact of personalised risk prediction must be collected for them to be widely implemented at pace in clinical practice. With these points in mind, we have designed the randomised controlled trial, described below.

## 2. Materials and Methods

### Study Design

This study is a multicentre randomised control trial across clinical-genetics services based in the UK and the USA. Women who have inherited a familial PV in *BRCA1, BRCA2, PALB2, CHEK2* or *ATM* will be randomised 1:1 into the intervention arm (personalised risk calculation), or the control arm (standard risk calculation), by stratified block randomisation (see section below). See Figure 1, for an overview of the study design.

## 3. Intervention (Personalised Risk Calculation)

Personalised risk calculations will be provided by the CanRisk tool (www.canrisk.org). CanRisk is a multifactorial-cancer-risk-prediction tool that combines genetic (e.g., rare genetic susceptibility variants and common genetic susceptibility variants in terms of a polygenic risk score (PRS)), family history, lifestyle and hormonal risk factors, to calculate the future risk of developing breast and/or epithelial ovarian cancer as well as the risk of being a carrier of a pathogenic variant [16,17]. The predicted cancer risks have been validated in several independent studies [26,27]. The CanRisk tool (see Figure 2, Figure 3 and Figure 4) was originally designed for use by healthcare professionals in a variety of settings [19] and is acceptable for use in clinical practice, particularly in the genetics setting [20].

## 4. Primary and Secondary Outcomes

The primary outcome for this study is both the type and the timing of risk management options (surveillance, chemoprevention, surgery) taken up over the course of the study (i.e., 12 months). The type of risk management options planned to be taken up in the future (i.e., beyond the end of the study) will be collected as a secondary outcome measure. Other secondary outcomes consist of informed decision-making about risk management options (measured by combining objective knowledge, attitude and behaviour [28]), women’s understanding of the test result [29] and the psychosocial impact (including cancer worry [30], anxiety [31] and quality of life [32]). Information on women’s use of health services will also be captured in order to perform a cost-utility analysis. Qualitative research methods offer important insights for the evaluation of health interventions and are increasingly being used as part of RCTs to strengthen the reliability and applicability of experimental findings to real-world settings [33,34,35,36]. As such, we plan to conduct semi-structured qualitative interviews with patients and staff, to better understand the acceptability and implementation of personalised risk calculations in clinical-genetics services.

## 5. Study Setting

This study will take place through clinical-genetics services based in the UK and USA. Initially, this will include Cambridge University Hospital (catchment area of 3,000,000) and Manchester University NHS Foundation Trust (catchment area of 5,000,000) in the UK and Stanford Cancer Institute (catchment area of 8,000,000) in the USA, with the capacity to expand to other clinical-genetic services, if needed. Women will be recruited through each clinical-genetics service and will remain in the clinical-genetics’s pathway throughout their participation in the study.

## 6. Participant Recruitment

Women will be recruited during the triage stage of their referral to clinical genetics; women will have been referred by healthcare professionals from primary care, breast surgery or family history clinics or will have self-referred because a family member has been found to have a PV in *BRCA1, BRCA2, PALB2, CHEK2* or *ATM*. Women will be assessed by the triaging healthcare professional(s), using the eligibility criteria, and flagged to the project coordinator.

## 7. Sample Size

We aim to recruit 1200 participants across the sites over the three years; approximately 600 will be randomised into the study (there is a 50% chance of those recruited having a PV in *BRCA1, BRCA2, PALB2, CHEK2* or *ATM*). We will assess whether there is a significant difference in uptake of RRM, at 12 months. When taking into account the expected distribution of PV carriers in the five genes within our clinical population, the uptake of RRM in *BRCA1/2* carriers and among women in different risk categories [37] and the expected risk distribution among the study participants based on the multifactorial BOADICEA v.6 model (including PRS) [38], the expected uptake of RRM in the intervention arm would be approximately 20%. Therefore:

To detect a difference of 5% in the uptake of RRM between the intervention and control arm, at a power of 80% and a 5% significance level, the sample size required in each arm is 924.

To detect a difference of 7.5% in the uptake of RRM between the intervention and control arm, at a power of 80% and a 5% significance level, the sample size required in each arm is 388.

To detect a difference of 10% in the uptake of RRM between the intervention and control arm, at a power of 80% and a 5% significance level, the sample size required in each arm is 204.

## 8. Eligibility Criteria

Women will be eligible for inclusion if they are: female, aged ≥18, undergoing predictive testing for a PV in *BRCA1, BRCA2, PALB2, ATM* or *CHEK2,* and able to give informed consent. Women will not be eligible for inclusion if they have a previous history of breast cancer or ovarian cancer.

## 9. Randomisation

Women will be randomised 1:1 via block stratification based on their age and the risk classification of the gene (moderate (*ATM, CHEK2*) or high (*BRCA1, BRCA2, PALB2*)). Block-allocation sequences will be computer-generated and shared with a non-participant-facing team member. The next sequence allocation will be shared at the time of each participant’s randomisation, for concealment purposes. It is not possible to blind the allocation group from the research team as additional testing needs to be ordered for women in the intervention arm of the study. Group allocation will not explicitly be shared with the participant, however, it may be inferred from their results letter, where it will either give a range risk figure for breast and ovarian cancer (i.e., 44–63% lifetime risk of breast cancer), or a personalised risk figure (e.g., 45% lifetime risk of breast cancer). The study team does not foresee any circumstances in which a patient would need to be unexpectedly unblinded.

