## 11. Data Analysis

Descriptive statistics will be used to summarise participants’s demographic characteristics. Univariate and multivariable analyses (linear and logistic regression) will be applied, taking into account the study arm and place of care (UK vs. USA). The multivariable models will adjust for the demographic characteristics reported at the beginning of the study. Multilevel models will be considered to investigate differences attributed to specific participant characteristics.

Health economic analysis will take the form of a lifetime cost-utility analysis, with health outcomes expressed as quality-adjusted life-years (QALYs), conforming to methods recommended by NICE [42]. Changes in health-related quality-of-life will be measured using the SF-6D derived from the SF-12 data [32], and modeling will be used to extrapolate lifetime costs and benefits.

Qualitative data collected through semi-structured interviews with patients and staff will be analysed deductively using thematic analysis [43], drawing from Sekhon’s Theoretical Framework of Acceptability (TFA; [44]) and the Consolidated Framework for Implementation Research (CIFR; [45]). Patient and staff data will be analysed separately but data from the UK and USA will be combined in order to compare and contrast between the different health settings.

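### Gene risk class is a randomisation stratum but is not in the stated adjustment set, which costs some precision on RRM uptake

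*Protocol article*

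**What the plan says.** **Randomisation (section 9).** "Women will be randomised 1:1 via block stratification based on their age and the risk classification of the gene". The classes are moderate (ATM, CHEK2) and high (BRCA1, BRCA2, PALB2). Country is not named as a stratum.

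**Analysis (section 11).** Linear and logistic regression are planned, "taking into account the study arm and place of care (UK vs. USA"). The covariate rule follows: "The multivariable models will adjust for the demographic characteristics reported at the beginning of the study". One further sentence leaves other models open: "Multilevel models will be considered to investigate differences attributed to specific participant characteristics". Gene risk class is named in none of these.

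**Gene class and surgery (section 1).** For moderate-risk variants, "the emphasis is more on surveillance and chemoprevention than surgical-risk reduction". A CHEK2 or ATM "carrier is generally quoted a lifetime risk of 20–30% and not offered BRRM".

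**Sizing (section 7).** The calculation concerns RRM uptake at 12 months. It draws on the expected spread of carriers over the five genes and concludes that "the expected uptake of RRM in the intervention arm would be approximately 20" per cent. About 600 women are to be randomised.

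**The concern.** Stratified randomisation balances gene class between the arms, so differences in uptake between classes no longer add to the random error of the arm comparison. A model without gene class still counts those differences as error. Its standard error is then larger than the design warrants, its confidence interval too wide and its p-value too large on average.

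The article treats gene as a driver of the outcome in three places: the clinical background, the derivation of expected uptake, and the choice of strata. The stated model does not follow through. The trial has little power to spare: about 300 women per arm, against the 388 that the article gives for a 7.5-point difference.

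**Working it through.** **1. The plan's own figures.** Pooled two-sided formula: n per arm = [1.96·√(2p̄(1−p̄)) + 0.8416·√(p₁(1−p₁)+p₂(1−p₂))]² / (p₁−p₂)², with p₁ = 20% (intervention) and p₂ below it (control).

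| Difference | Control uptake | Recomputed n per arm | Stated n per arm | Unadjusted power at 300 per arm |
|---|---|---|---|---|
| 5 points | 15% | 906 | 924 | 36% |
| 7.5 points | 12.5% | 379 | 388 | 70% |
| 10 points | 10% | 199 | 204 | 93% |

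The stated sizes reproduce within 3%, and only with control uptake below 20%. They are not in dispute. They fix the reading of the 20%: it is uptake in the intervention arm, not overall.

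**2. Strata against model terms.**

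| Factor | Stratum | In the stated model |
|---|---|---|
| Age | yes | probably, as a demographic |
| Gene risk class | yes | not named |
| Country | no | yes |

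The gap is gene risk class.

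**3. Share of outcome variance due to gene class.** Let m be the moderate-gene share, u_m and u_h uptake in moderate- and high-risk carriers, and P overall uptake. Then u_h = (P − m·u_m)/(1 − m), R² = m(1−m)(u_h − u_m)² / [P(1−P)], and the equivalent gain in sample size is 1/(1−R²) − 1.

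With 20% against 12.5% uptake and 1:1 allocation, P = (0.20 + 0.125)/2 = 0.1625 and P(1−P) = 0.1361. The values of m and u_m are assumptions, because the article gives neither.

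| m | u_m | u_h | R² | Equivalent gain in n | On 600 women |
|---|---|---|---|---|---|
| 0.20 | 0.05 | 0.191 | 0.00316/0.1361 = 0.023 | 2.4% | about 14 |
| 0.30 | 0.02 | 0.224 | 0.00870/0.1361 = 0.064 | 6.8% | about 41 |
| 0.40 | 0.02 | 0.258 | 0.01354/0.1361 = 0.099 | 11.1% | about 66 |

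**4. Simulation.** Logistic regression on 600 women, allocation balanced within gene class, arm and country in both models, gene class in one. There were 6,000 replicates for type I error and 3,000 for power. The inputs are again assumed: four mixes with intervention-arm uptake averaging 20%, and a common odds ratio for control against intervention of (0.125/0.875)/(0.20/0.80) = 0.571.

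| High-risk share | Uptake high / moderate | Type I error without / with gene class | Power without / with gene class |
|---|---|---|---|
| 80% | 22% / 12% | 5.0% / 5.1% | 69.9% / 70.3% |
| 75% | 25% / 5% | 4.4% / 5.0% | 67.8% / 69.2% |
| 60% | 30% / 5% | 3.3% / 4.4% | 64.9% / 68.1% |
| 50% | 35% / 5% | 3.1% / 4.9% | 62.3% / 66.4% |

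The type I error without gene class is at or below 5% throughout, and the power lost is between 0.4 and 4.1 points. Monte Carlo error is about 0.3 points for type I error and 0.9 for each power. Age was not modelled, and country had no effect on the outcome. Because a common odds ratio is applied within each class, control uptake over both classes is 12.5% to 13.2%, so the absolute difference shrinks a little down the table. The two models in each row are still compared on the same data.

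**The case against.** **The covariate list may be in the full plan.** This is a condensed article. It names a category of covariates, not a closed list, and does not label a primary model. Stratification factors may well appear in the full protocol or SAP, and nothing in section 11 says they will be left out. This limits the weight of the point but does not remove it: the article does state an adjustment rule, and on its plain wording gene class falls outside it. The sentence on multilevel models is only a possibility, with no characteristic named.

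**The effect is mild.** This stands. The test is conservative, and in the weakest scenario almost nothing is lost.

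Several stronger readings are tempting, and the article does not support them:

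- *Gene class could not be a baseline covariate because it is known only after testing.* Women are referred because a relative carries a known variant (section 6) and are tested for that familial variant (sections 8 and 10). The gene is therefore known at referral; testing settles carrier status only. Gene class falls outside the rule because it is not a demographic.
- *Gene class is the strongest predictor of RRM.* Section 1 supports a link, but no uptake by class or by age is given, so no ranking is possible.
- *Country should have been a stratum because it is in the model.* Adjusting for a factor that was not stratified is ordinary practice. With 300 per arm and an even country split, the chance difference in country share has SD √(2 × 0.25/300) = 0.041, about 4 points, and the model adjusts for it. A further stratum is a preference.
- *The gain would be about 4–16% of sample size.* The formula in step 3 gives that range (3.6% to 15.6%) if 20% is taken as overall uptake, but section 7 gives 20% for the intervention arm.

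**Conclusion.** The point holds as a modest one about efficiency. The stated adjustment set omits gene risk class, a stratification factor that the article itself ties to the offer of mastectomy. The expected result is a standard error somewhat too large and a conservative test for RRM uptake. A reader might infer bias or an inflated false-positive rate; neither follows, and no simulated scenario showed type I error above its nominal level without gene class.

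Both estimates of size, 2–11% of the sample size and about 0 to 4 points of power, rest on assumed carrier shares and uptake by class that the article does not give. The direction depends only on gene class being balanced by design and related to uptake. If moderate-risk carriers are few, or uptake differs little between classes, the loss is close to nil.

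**What to change.** In section 11, name the covariates of the model for RRM uptake at 12 months: study arm, age, gene risk class (moderate/high) and country (UK/USA).

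Preferably, report the arm effect from that model as a covariate-standardised risk difference with 95% CI. Section 7 sizes the trial in percentage points, and adding a prognostic covariate to a logistic model changes what the odds ratio measures. This is a reporting improvement and does not follow from the stratum mismatch alone.

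The cost is one or two sentences, written before the analysis. Gene class is recorded for randomisation, so no new data are needed. The strata can stay as they are. If the full protocol or SAP already lists gene class, the article's wording need only be brought into line with it.

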## 10. Study Procedure

Women will be assessed for eligibility at the point of triage when referred to the clinical-genetics service. Once identified as eligible, they will receive an information pack containing details about the study, as well as a link to the online consent form. After completing and submitting the online consent form, the participant will receive a baseline questionnaire (Supplementary Material File S1), to be completed before attending their standard clinical-genetics appointment. The baseline questionnaire collects data on lifestyle, hormonal factors and family history. It also contains a range of validated scales, measuring numeracy [39], intolerance of uncertainty [40], perceived levels of absolute and comparative risk [41], cancer worry [30], anxiety [31] and quality of life [32]. Participants will also be asked to provide information about their general health and any recent interactions with healthcare providers.

Participants will undergo predictive/pre-symptomatic genetic testing, as per standard clinical procedure, specific for each site. Of those participants whose genetic test shows that they have inherited the familial PV in *BRCA1, BRCA2, PALB2, ATM* or *CHEK2* (approximately 50% of all individuals tested), half will be randomised into the intervention arm of the study, which includes running the polygenic risk panel on their stored DNA sample. Once this result is available, it will be combined with the patient’s clinical-genetics result and their family history of cancer, as well as their lifestyle and hormonal factors using the CanRisk tool. The CanRisk tool will provide a personalised risk estimate which will be shared with the patient via clinical letter. Women who are randomised into the control arm of the study will receive the standard generalised risk estimate at approximately the same time point (post results) as those in the intervention arm of the study.

After getting the final risk assessment via clinical letter, participants will receive follow-up questionnaires (Supplementary Material File S2), at one, three and twelve months. Questionnaires will collect data on the uptake of risk management options (actual and planned) as well as their knowledge and attitude towards these options. We will also ask participants about their understanding of the test result ([29]; at one month only), perceived levels of absolute and comparative risk [41], cancer worry [30], anxiety [31] and quality of life [32]. As a baseline, participants will also be asked to give information about their general health and any recent interactions with healthcare providers. Participants (*n* = 40; 20 in the UK and 20 in the USA) and staff (*n* = 20; 10 in the USA and 10 in the UK) will be invited to participate in a 30–60 min semi-structured video/audio interview, recorded face-to-face or online (via Zoom/MS Teams). Interviews will explore their experiences of taking part in the study, with a view to understanding whether personalised risk estimates are acceptable and feasible for use in clinical care.

